### Interim analyses {21b}

Due to the low risks associated with the interventions and well-known beneficial effects of physical activity and nutritional counseling, interim analyses are not planned.

### Methods for additional analyses (e.g., subgroup analyses) {20b}

An exploratory analysis will be conducted through the principal component analysis (PCA), in order to highlight any subgroups showing a homogeneous response pattern. Additional exploratory analyses will also be performed using participants’ characteristics (e.g., age, fitness status, physical activity level, and metabolic and clinical profile) as covariates to assess possible underlying confounding variables on the primary and secondary outcome results.

### Methods in analysis to handle protocol non-adherence and any statistical methods to handle missing data {20c}

This study will employ a per-protocol analysis in which missing data will not be imputed. Sensitivity analyses will be performed to assess the robustness of the results based on quantitative and qualitative levels of adherence to the exercise protocol. The main statistical analyses will be performed without considering the exercise protocol adherence. In accordance with the available literature (see Hawley-Hague et al. [31] for a methodological review on this topic), the three sensitivity analyses will be performed by including, in the statistical analysis, only the participants who completed at least 65, 70, and 75% of the total training sessions exercising at both the prescribed intensities (i.e., with an average exercise intensity of each session within 4 bpm of the prescribed HR [21]) and durations (i.e., with an exercise session duration within 5 min of the prescribed duration). The qualitative reasons for withdrawal from the trial or non-adherence to the exercise protocol will be recorded. Finally, to assess if the missing data and non-adherence to the exercise protocol are at random, exploratory analyses will be performed to assess the presence of patterns among the missing data, exercise protocol non-adherence, participants’ characteristics, and group allocation.

Trial retention will be scored as the rate of drop-out in the intervention group after signing informed consent for the study.

Cohort retention drop-out in the intervention and control group will be defined as withdrawal from the cohort and/or non-response to the regular cohort measurements and will be scored for both groups.

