### Criteria for discontinuing or modifying allocated interventions {11b}

Participants will be withdrawn from the trial if they are considered not suitable for non-competitive physical activity. The following criteria will be considered: disabling pneumological, cardiological, neurological, orthopedic comorbidities, or mental illnesses that affect the exercise performance; treatment with beta blockers, non-dihydropyridine calcium channel blockers, or amiodarone due to their potential effect on heart rate response to exercise; treatment with antidepressant drugs; and recurrence diagnosis.

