### Relevant concomitant care permitted or prohibited during the trial {11d}

Information on concomitant medication (prescription, over-the-counter, herbal and naturopathic remedies, etc.) will be collected at the beginning and during the study.

The research team will not interfere with the medication prescription, which will be chosen by the health care providers (i.e., oncologist and general practitioner). If the concomitant medications are incompatible with the inclusion criteria of the study, the participants will be excluded from the study.

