### Sample size {14}

The sample size was calculated with the aim of verifying the differences between the QoL changes in the two groups (i.e., intervention and control arm), after 3 months of intervention.

The QoL expected improvement in the experimental group at 12 weeks is 15.1 ± 17.7, while in the control arm, it is 6.1 ± 17.1 [24]. Using a *t*-test for independent samples, with an alpha of 0.05 and statistical power of 0.80, to find differences in QoL improvements between the two groups at the end of the intervention, 60 participants per group will be needed. Considering an expected drop-out of 30%, a total of 172 patients will be recruited. The sample size was calculated using Stata statistical software (StataCorp. 2013. Stata Statistical Software: Release 13. College Station, TX: StataCorp LP).

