## Statistical methods

### Statistical methods for primary and secondary outcomes {20a}

A mixed-design ANOVA will be used to compare the changes over time (from T1 to T2, within factor) in the primary outcome between intervention and control arms (between factor). The sample size was calculated to test the hypothesis of no differences between the changes in the primary outcome of the two groups (i.e., interaction effect of the between and within factors of the mixed-design ANOVA). If a significant effect is found, post hoc pairwise comparisons will be used.

Secondary outcomes will be analyzed using repeated measures MANOVA models, with difference-based contrasts.

For all tests, a 2-sided *α* level of significance of 0.05 will be used and, if necessary, the *α* level inflation due to multiple tests will be accounted for by using the appropriate correction (e.g., Bonferroni, false discovery rate, etc.). The statistical test assumptions will be assessed and, if not met, either data transformation or alternative statistical methods (e.g., GEE, non-parametric analyses, etc.) will be performed.

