Moreover, in the present project, although it is recommended that exercise programs include resistance exercises [8, 20], the participants of both groups will solely receive generic indications regarding the importance and guidelines of resistance exercises and flexibility training during the counseling sessions, but they will not receive any supervision or prescription for those two exercise modalities. Therefore, the inferences on the possible short- and long-term differences between the two arms, hence the effect of the mixed directly and remotely supervised exercise intervention, will only be applicable and valid for aerobic exercise; hence, future studies should assess the efficacy of these types of interventions and supervisions in exercise programs involving both aerobic and resistance exercise or resistance exercise only.

Additionally, it is worth noting that RCT interventions in the field of exercise oncology have several limitations, such as drop-out and loss of follow-up of patients during the entire course of the study. For this reason, we estimate an expected drop-out of 30% for a total of 172 patients after the 12-week interventions, which will probably increase over the 2 years of follow-up. To ensure that the drop-out rate is not affected by the present study design and consequently affects the results of the present study, trial retention will be scored as the rate of drop-out after signing informed consent for the study and registered for both groups. Then, exploratory analyses will be performed to assess if several factors (e.g., trial arm, clinical, and characteristics) affected the drop-out rate.

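### The primary QoL analysis is labelled per-protocol but reads as a complete-case comparison that omits about 52 of 172 randomised women, and no planned analysis tests assumptions about their missing outcomes

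*Protocol article*

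**What the plan says.** All references are to the protocol article.

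- **Analysis population, {20c}.** The section opens with "This study will employ a per-protocol analysis in which missing data will not be imputed". Two sentences later it says "The main statistical analyses will be performed without considering the exercise protocol adherence". Three sensitivity analyses are then restricted to "only the participants who completed at least 65, 70, and 75% of the total training sessions", with further conditions on session intensity and duration.
- **Primary model, {20a}.** "A mixed-design ANOVA will be used to compare the changes over time (from T1 to T2, within factor) in the primary outcome". GEE appears only as one possible alternative if test assumptions fail.
- **Drop-out, Sample size {14}.** "Considering an expected drop-out of 30%, a total of 172 patients will be recruited". The Discussion places this loss at the end of the intervention: "we estimate an expected drop-out of 30% for a total of 172 patients after the 12-week interventions", and expects it to grow over the two-year follow-up.
- **Withdrawal by the trial, {11b} and {11d}.** "Participants will be withdrawn from the trial if they are considered not suitable for non-competitive physical activity". The listed grounds include antidepressant treatment and a diagnosis of recurrence. On other medicines: "If the concomitant medications are incompatible with the inclusion criteria of the study, the participants will be excluded from the study".
- **Missing-data checks, {20c} and Discussion.** Reasons for withdrawal are recorded. Exploratory analyses look for patterns in missing data and drop-out, including by arm.

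The article names no as-randomised analysis set and defines no per-protocol set.

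**The concern.** A per-protocol analysis selects on adherence, and an analysis that disregards adherence does not. The article uses the first name and describes the second, so a later report could cite {20c} for either.

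The larger issue remains once the label is set aside. A two-time-point ANOVA without imputation drops every woman who lacks a T2 score. The comparison is then conditioned on staying in the trial, which happens after randomisation. Three features make this matter here:

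- Patients know their allocation and report the primary outcome themselves.
- Only the intervention arm carries the training burden, so unequal drop-out is credible.
- Several withdrawal grounds (antidepressants, recurrence, disabling illness) plausibly go with poor QoL.

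At stake is whether the reported QoL difference estimates the effect of being assigned to the programme, or mixes that effect with who stayed.

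**Working it through.** **1. The plan's own figure.** Inputs from {14}: mean changes 15.1 (SD 17.7) and 6.1 (SD 17.1), alpha 0.05, power 0.80; {20a} makes tests two-sided.
- Difference: 15.1 − 6.1 = 9.0. Pooled SD: √((17.7² + 17.1²)/2) = 17.40.
- The t-test solution is 59.67, so 60 per arm (power 0.802).
- 60/0.70 = 85.7, so 86 per arm and 172 in total.

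The sample size reproduces and is not at fault. It also shows that the test is designed to rest on about 120 women: 0.30 × 172 = 51.6, about 52, are expected to be absent.

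**2. Which reading fits.** If adherence selection applied to the primary analysis, the statement that the main analyses disregard adherence would be false and the three sensitivity analyses would have little to add. If per-protocol is loose wording for women with complete data, analysed as allocated, the rest of {20c}, {20a} and {14} fit together. The second reading is the more coherent. T2 is taken to be the 3-month assessment, since {14} sizes the trial on change after 3 months.

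**3. Possible bias (illustration; the article gives no split of drop-out by arm).** Assume each woman has a standard normal tendency to stay, correlated ρ with her QoL change, and that the lowest fraction p leaves. Stayers' mean change then shifts by ρ × SD × λ(p), where λ(p) = φ(z_p)/(1 − p). The complete-case bias is

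ρ × (17.7 λ(p_I) − 17.1 λ(p_C)).

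Values: λ(0.20) = 0.350, λ(0.25) = 0.424, λ(0.30) = 0.497, λ(0.35) = 0.570, λ(0.40) = 0.644. Rejection under a true null uses SE = √(17.7²/n_I + 17.1²/n_C) with n = 86(1 − p).

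| Drop-out, intervention/control | Bracket | Bias, ρ = 0.3 | Bias, ρ = 0.5 | SE | Two-sided rejection |
|---|---|---|---|---|---|
| 40%/20% | 11.40 − 5.99 = 5.41 | +1.62 | +2.71 | 3.21 | 8.0% to 13.4% |
| 35%/25% | 10.09 − 7.25 = 2.84 | +0.85 | +1.42 | 3.18 | 5.8% to 7.3% |
| 30%/30% | 8.79 − 8.49 = 0.30 | +0.09 | +0.15 | 3.17 | 5.0% |
| 20%/40% | 6.20 − 11.01 = −4.82 | −1.44 | −2.41 | 3.20 | 7.4% to 11.7% |

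Against the planned 9 points, the first row is 1.62/9 = 18% to 2.71/9 = 30%. Allowing for the smaller variance among stayers raises its upper rejection figure to about 15%. In the last row almost all excess rejections favour control: false claims of benefit fall to about 0.3 to 0.8%, against 2.5% nominal.

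**4. Whether existing analyses cover this.** Controls have no training sessions, so the 65, 70 and 75% thresholds can remove only intervention women; they add selection. The exploratory checks can show that drop-out differs by arm, but they leave the estimate unchanged. Nothing planned varies the assumption about the missing outcomes.

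**The case against.** The best defence is that {20c}, read as a whole, is workable. Adherence is disregarded in the main analyses, adherence cut-offs stay in sensitivity analyses, {20a} fixes model and time points, and {14} allows for the loss. This stands in part: it settles the adherence wording and leaves a wrong label plus a complete-case choice. A reader might infer that the primary comparison is wholly undefined. The documents do not support that.

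A reader might also infer that removing non-adherent women cuts power to 0.65–0.73. That needs adherence selection in the primary analysis and an assumed 25 to 45% of intervention completers removed. {20c} places that selection in sensitivity analyses, so no loss of power is claimed here.

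The bias depends on assumptions. The article gives a single 30% figure, and equal drop-out with the same mechanism gives almost no bias. That stands, and so does the point that more drop-out among controls would make a false claim of benefit less likely.

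Finally, a likelihood-based model assumes data missing at random, whereas the illustration makes drop-out depend on the outcome itself. This also stands. In a simulation of the 40%/20% case with women who leave before T2 and never return, such a model kept about 77 to 100% of the bias, for assumed baseline–change correlations from −0.5 to 0.

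The article's retention measures and pattern checks are useful, but they do not correct an estimate.

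**Conclusion.** The point holds in a limited form. {20c} misnames its analysis. On its most coherent reading the primary result is a complete-case comparison as allocated, resting on about 120 of 172 randomised women, with no as-randomised analysis named and no analysis that tests assumptions about the missing outcomes. This is not a detail left to an unseen analysis plan, because the article itself sets the rule.

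The wording conflict and the count of about 52 absent women follow directly from the text. The size of any bias does not. It is about +1.6 to +2.7 points at an assumed 40%/20% split, about +0.9 to +1.4 at 35%/25%, and near zero at equal drop-out with the same mechanism, all for an assumed correlation of 0.3 to 0.5. A reader might conclude that 30% drop-out by itself inflates the type I error; it does so here only if drop-out is both informative and different between arms. The change is still needed before analysis, because the rule decides who counts in the headline result of an open-label trial with a self-reported outcome.

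**What to change.** - **{20c}, population.** Delete the per-protocol label. State that the primary analysis compares all randomised women in the arm assigned, whatever their adherence.
- **T2 collection.** Seek the T2 QLQ-C30 from women who stop the programme or are withdrawn, where they consent. Reconcile {11b} and {11d} with this, making clear whether leaving the intervention also ends data collection.
- **{20a}, model.** Use a likelihood-based repeated-measures model of all available QLQ-C30 values, including the 6-, 12- and 24-month follow-up that the Discussion foresees, with the 3-month contrast primary. This lets a woman who misses only T2 contribute.
- **Sensitivity.** Add a delta-adjusted missing-not-at-random analysis, with the shift allowed to differ by arm, because the likelihood model alone does not remove outcome-dependent drop-out bias.
- **Adherence analyses.** Label the 65, 70 and 75% analyses as supportive and note that the session threshold can restrict only the intervention arm.

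**Cost.** Wording, a little more analysis work, and effort to obtain one questionnaire after withdrawal; no more patients. The expected difference may be smaller than 9 points. As an illustration, if the 30% who drop out gained nothing over control, it would be 0.7 × 9.0 = 6.3 points, and power with 86 per arm fully followed would be about 62 to 65%. The team should weigh this when restating the target effect.

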**Methods:**

One hundred seventy-two BC survivor women, aged 30–70 years, non-metastatic, stage 0–III, non-physically active, 6–12 months post-surgery, and post chemo- or radiotherapy, will be recruited in this study. Women will be randomly allocated to the intervention arm (lifestyle recommendations and MoviS Training) or control arm (lifestyle recommendations). The MoviS training consists of 12 weeks of aerobic exercise training (2 days/week of supervised and 1 day/week of unsupervised exercise) with a progressive increase in exercise intensity (40–70% of heart rate reserve) and duration (20–60 min). Both arms will receive counseling on healthy lifestyle habits (nutrition and exercise) based on the World Cancer Research Fund International (WCRF) 2018 guidelines.

The primary outcome is the improvement of the QoL. The secondary outcomes are improvement of health-related parameters such as Mediterranean diet adherence, physical activity level, flexibility, muscular fitness, fatigue, cardiorespiratory fitness (estimated maximal oxygen uptake), echocardiographic parameters, heart rate variability (average of the standard deviations of all 5 min normal to normal intervals (ASDNN/5 min) and 24 h very low and low frequency), and metabolic, endocrine, and inflammatory serum biomarkers (glycemia, insulin resistance, progesterone, testosterone, and high-sensitivity C-reactive protein).

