### Intervention description {11a}

Patients will be randomly allocated to the intervention arm (lifestyle recommendations and MoviS Training) or the control arm (lifestyle recommendations). The MoviS training consists of 3 months of aerobic exercise training (2 days/week of directly supervised by an exercise specialist and 1 day/week of remotely supervised exercise) with a progressive increase in exercise intensity (40–70% of heart rate [HR] reserve [HRR]) and duration (20–60 min). Even though several methods can be used to tailor exercise intensity [19], in the present trial, exercise intensity will be prescribed using percentages of HRR corresponding to moderate and vigorous intensity categories as suggested by the current breast cancer-specific guidelines [8, 20]. Each session will start with a 5-min warm-up period, which will be used to gradually reach the target exercise intensity (i.e., HR). Additionally, to account for several physiological adjustments that happen during prolonged aerobic exercises (e.g., cardiovascular drift), heart rate responses will be monitored throughout the training sessions and external exercise intensities (e.g., bike wattage or treadmill speed and grade) will be adjusted to maintain the target HR throughout each training session [21]. Particular focus will be given to participants’ compliance with the prescribed exercise intensity (i.e., target HR) and to their ability to maintain it while training under the direct supervision of an exercise specialist (2 days/week) and autonomously (1 day/week), Indeed, HR monitors will be given to the participants allocated to the intervention arm, who will be instructed on how to use them. Then, the intervention arm participants will be educated on how to independently reach and maintain the desired exercise intensity (i.e., target HR) by means of personalized feedback given by an exercise specialist. During the directly supervised sessions, personalized feedback on how to increase compliance with the desired exercise intensity will be given live, in real-time, based on the HR responses to the exercise, whereas, regarding the remotely supervised sessions performed autonomously by the participants, the feedback will be given after the completion of the training sessions according to the training log, which will include the HR responses to the training session. The directly supervised sessions will be performed in a gym using treadmills or stationary bikes, whereas the remotely supervised sessions will be performed indoors or outdoors according to the possibilities and preferences of each participant. Regardless of the exercise modality, the external exercise intensities (e.g., walking speed and grade or cycling wattage) will be adjusted to reach and maintain the prescribed target HR. Group training sessions and continuous supervision by an exercise specialist, either directly or remotely, will be used as a motivational tool in which adherence will be mainly driven by intrapersonal (e.g., health-related) and interpersonal motives (e.g., empathy with exercise specialists and enjoyment).

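### The adherence sensitivity analyses filter on a criterion that only the intervention arm can meet, so they lose the randomised comparison and cannot serve as the robustness check

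*Protocol article*

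**What the plan says.** The section on non-adherence and missing data {20c} first sets the main analysis apart from adherence: "The main statistical analyses will be performed without considering the exercise protocol adherence". It then gives the filtered analyses their purpose: "Sensitivity analyses will be performed to assess the robustness of the results based on quantitative and qualitative levels of adherence to the exercise protocol". There are three of them, and each keeps "only the participants who completed at least 65, 70, and 75% of the total training sessions exercising at both the prescribed intensities" and durations. A session counts if it was performed "with an average exercise intensity of each session within 4 bpm of the prescribed HR" and "with an exercise session duration within 5 min of the prescribed duration".

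The intervention description {11a} shows where these quantities exist. Controls receive lifestyle recommendations without MoviS training. Target heart rates, training logs and specialist feedback belong to the training programme, and "HR monitors will be given to the participants allocated to the intervention arm". The article gives no rule for how controls enter the filtered analyses.

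The statistical methods section {20a} tests the primary outcome by the interaction of arm and time (T1 to T2) in a mixed-design ANOVA.

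**The concern.** The inclusion rule is worded for participants in general, but it can be evaluated in one arm only. Applied to everyone, it leaves no comparator. Applied to exercisers only, it removes women from one arm on something that happened after randomisation and leaves the other arm whole. Women who complete most sessions at the prescribed heart rate and duration may differ from the rest in ways that also bear on QoL change. No matching group of would-be adherers can be picked out among the controls.

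This matters because the plan uses these analyses to judge whether the result is robust. Three similar estimates, or estimates that grow with the cut-off, could be cited as confirmation or as dose-response, although selection could produce the same picture.

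**Working it through.** **Step 1: who can meet the rule.** The abstract gives 12 weeks of training with 2 supervised days and 1 unsupervised day per week: 12 × 3 = 36 sessions. The cut-offs are 0.65 × 36 = 23.4, 0.70 × 36 = 25.2 and 0.75 × 36 = 27, so at least 24, 26 and 27 compliant sessions. Controls have no prescribed sessions, so none can reach any cut-off.

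**Step 2: the two readings.**
- Literal: 0 controls remain, and an arm-by-time interaction cannot be estimated from one arm.
- Probable: selected exercisers against all controls. The interaction can be estimated, but the groups compared are no longer those formed by randomisation.

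**Step 3: what agreement across cut-offs can show.** Every woman who passes 75% also passes 70% and 65%. The subsets are nested, and they differ only by women with 24 to 26 compliant sessions. All three share the same selection mechanism and nearly the same women, so they would tend to agree whether or not selection bias is present.

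**Step 4: the plan's own figures.** The sample size section {14} gives changes of 15.1 (SD 17.7) and 6.1 (SD 17.1), a difference of 9.0. The root mean square SD is √((17.7² + 17.1²)/2) = 17.40. The normal approximation gives 2 × (1.960 + 0.842)² × 17.40² / 9.0² = 58.7, so 59 per arm; the noncentral t gives 60 per arm (power 0.802). With 30% drop-out, 120/0.70 = 171.4, so 172. The stated sample size reproduces.

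**Step 5: possible size under the probable reading, with a true training effect of zero.** Two inputs are assumptions and do not come from the documents: the correlation ρ between adherence and QoL change (0.1 to 0.4), and the fraction p of the 60 evaluable exercisers who are excluded (25 to 45%). If adherence and QoL change are jointly normal and the least adherent fraction p is removed, the mean change in the retained women shifts by

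shift = ρ × 17.7 × φ(z_p) / (1 − p),

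where z_p is the p-quantile of the standard normal and φ its density. The factor φ(z_p)/(1 − p) is 0.424, 0.570 and 0.720 for p = 0.25, 0.35 and 0.45.

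| Excluded | ρ = 0.1 | ρ = 0.2 | ρ = 0.3 | ρ = 0.4 |
|---|---|---|---|---|
| 25% | 0.75 | 1.50 | 2.25 | 3.00 |
| 35% | 1.01 | 2.02 | 3.03 | 4.03 |
| 45% | 1.27 | 2.55 | 3.82 | 5.10 |

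These shifts are 8% (0.75/9) to 57% (5.10/9) of the planned difference. With 60 × (1 − p) exercisers against 60 controls, SE = √(17.7²/(60(1 − p)) + 17.1²/60), which is 3.44 at p = 0.25 and 3.79 at p = 0.45. The two-sided 5% test of the filtered comparison then rejects with probability of about 0.06 (ρ = 0.1, p = 0.25) to 0.27 (ρ = 0.4, p = 0.45). At ρ = 0 there is no shift; a negative ρ reverses the sign.

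**The case against.** The strongest reply has four parts.

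- **Only supplementary analyses are touched.** The main analysis ignores adherence, and no decision rule hangs on the filtered results. This stands. A reader might infer that the primary result is biased by the filter, or that the trial's false-positive rate is inflated; section {20c} rules that out. The rejection rates above belong to the filtered comparisons alone.
- **Controls are obviously meant to stay.** The planned interaction needs both arms, and only one arm has an exercise protocol to adhere to. This also largely stands: it would be too strong to say that the analyses have no comparator. But keeping the controls leads straight to the non-randomised comparison.
- **The sign and size of the bias are not established.** Nothing in the documents says that women who feel better adhere more. The criterion is partly technical: a woman who overshoots her target heart rate by more than 4 bpm also fails. This stands. It would also be too strong to predict an apparent dose-response. The 25 to 45% range is not tied to the three cut-offs, and a rise from 25 to 45% excluded would need 12 of 60 women (0.20 × 60) in a band of three session counts.
- **Selection is examined elsewhere.** Section {20c} plans exploratory analyses of patterns in non-adherence, and section {20b} plans covariate analyses. They may describe who adheres, but neither changes the filtered comparison.

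The point is not detail left to an analysis plan. The article itself fixes the rule, its cut-offs and its tolerances, and gives it the robustness role.

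**Conclusion.** The point holds for the three sensitivity analyses and goes no further. Their inclusion rule exists in one arm only. Under the workable reading they compare exercisers selected after randomisation with unselected controls, and agreement among nested subsets chosen in the same way cannot show robustness. This follows from the text and needs no assumed figure.

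The size is conditional. With a positive correlation of 0.1 to 0.4 and 25 to 45% of exercisers excluded, all assumed, the spurious difference is roughly 0.75 to 5 points against the planned 9. With zero correlation it vanishes, and with a negative one it runs the other way. The correction is worth making because it is cheap and removes an unsound basis for a conclusion.

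**What to change.** In section {20c}:

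1. State that all controls are retained in the adherence-restricted analyses.
2. Label those results descriptive.
3. Remove their role as the robustness check, and state that a trend across 65, 70 and 75% will not be read as dose-response.

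This costs a few sentences.

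If an adherence-adjusted effect is wanted, add one supportive estimate that keeps the randomised comparison: for example, two-stage least squares with randomised arm as instrument and the proportion of prescribed sessions completed as treatment received (zero for controls). State the exclusion assumption (allocation acts on QoL only through sessions completed) and the linearity assumption (benefit proportional to sessions completed). State also how missing outcomes are handled, since the plan expects 30% drop-out and does not impute.

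A complier-average effect with adherence cut at each threshold is less suitable. It assumes no benefit below the cut-off, and it divides the between-arm difference by the share above it, so it rises mechanically: a 9-point difference becomes 9/0.75 = 12.0, 9/0.65 = 13.8 or 9/0.55 = 16.4 as the adherent share falls.

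The optional model costs wider intervals and an untestable assumption. Its test largely repeats the between-arm test made without the filter, so it informs the size of effect more than robustness.
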